**Methods and analysis:**

VPT-II is a single-blind open-label randomised controlled trial of 2500 infants in three districts of Ho Chi Minh City, Vietnam. Eligible infants have no clinically significant maternal or perinatal history and are born at or after 36 weeks’ gestation. Participants are recruited at 2 months of age and randomly assigned (4:4:4:4:9) using block randomisation, stratified by district, to one of five groups: four intervention groups that receive PCV10 in a 0+1 (at 12 months) or 1+1 (at 2 and 12 months) schedule or PCV13 in the same 0+1 or 1+1 schedule; and a control group (that receives a single dose of PCV10 at 24 months). Participants are followed up to 24 months of age. The primary outcome is vaccine-type pneumococcal carriage at 24 months of age. Secondary outcomes are carriage at 6, 12 and 18 months of age and the comparative immunogenicity of the different schedules in terms of antibody responses, functional antibody responses and memory B cell responses.

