## Methods

### Study setting

The trial is conducted in three districts within Ho Chi Minh City, Vietnam (districts 4, 7 and 8). Districts are divided into communes, each of which has a health centre that provides preventive health services including EPI vaccines, along with primary healthcare services. The trial is conducted in one commune health centre in each district, with participants drawn from the surrounding communes within that district.

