### Sample size

The target sample size is 2500 with an allocation ratio of 4:4:4:4:9. This allocation ratio provides the greatest power for a total sample size of 2500 and results in target group sizes of 400 for each of the four different infant vaccination schedules (groups V–Y) and 900 for the control group (group Z). Sample size calculations are based on the primary outcome of effect on VT pneumococcal carriage at 24 months of age. For each of the four vaccination schedules compared with the unvaccinated control group, the proposed sample size provides 82% power to detect a 40% reduction in the vaccinated group, with a two-sided type I error rate of 5%. The sample size calculations assume 15% VT pneumococcal carriage among controls, based on data from our previous pneumococcal vaccine trial in Ho Chi Minh City,^20^ and 10% lost to follow-up.

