### Allocation

The allocation ratio of Groups V, W, X, Y and Z is 4:4:4:4:9. The first 200 participants enrolled into each of groups V–Y, and a randomly selected 200 of the first 450 participants concurrently enrolled into group Z, will go into the immunology sub-study. These participants (with the exception of group Z) will be further randomised into one of four subgroups (a, b c or d) in an equal allocation ratio (table 2). Randomisation will be conducted by a database manager in Australia, using a computer-generated list of random numbers in a block randomisation scheme stratified by district. The group allocation, and subgroup allocation where relevant, is contained within a sealed envelope at the study clinic. Participants are assigned to a study group by a study doctor, using the next available envelope. The envelopes are prepared and sealed in the study office in Vietnam, by staff with no involvement in the recruitment process.

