### Statistical methods

#### Analysis of primary and secondary outcomes

The primary outcome of VT carriage will be presented as a proportion (prevalence). VT carriage prevalence in each of the vaccinated groups (PCV10-type carriage for groups V and X and PCV13-type carriage for groups W and Y) will be compared with unvaccinated controls. Prevalence ratios (ratio of prevalence in each vaccinated group to prevalence in unvaccinated controls) with 95% CIs will be calculated, and groups compared using χ^2^ tests (two-sided p values reported). The primary endpoint is 24 months of age, with secondary endpoints of 6, 12 and 18 months of age. At 6 and 12 months of age, time points at which no swabs were collected from group Z, swabs from the 0+1 groups (groups V and W combined) will form the unvaccinated comparator.

Immunological outcomes will be summarised in terms of: geometric mean concentrations (GMCs) and the proportion with protective antibody levels (≥0.35 µg/mL)^22^ with 95% CIs for serotype-specific IgG data, geometric mean OIs (GMOIs) and the proportion with an OI ≥8^23^ with 95% CIs for OPA data, and the mean number of antibody secreting cells per 10^6^ PBMCs for polysaccharide-specific memory B cell data. GMC and GMOI ratios and risk differences with 95% CIs will also be calculated. Means will be compared using t-tests and proportions compared using Fisher’s exact tests.

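### Randomisation is stratified by district but the stated primary analysis is crude, so its test and intervals would be slightly conservative if carriage differs between districts

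*Protocol article*

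**What the plan says.** The protocol article describes the allocation twice. The abstract has infants "randomly assigned (4:4:4:4:9) using block randomisation, stratified by district", and the Allocation section has the database manager "using a computer-generated list of random numbers in a block randomisation scheme stratified by district". Study setting gives the strata: "The trial is conducted in three districts within Ho Chi Minh City, Vietnam (districts 4, 7 and 8", with one study clinic in each.

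The analysis is set out under Analysis of primary and secondary outcomes. The effect measure is "Prevalence ratios (ratio of prevalence in each vaccinated group to prevalence in unvaccinated controls) with 95% CIs will be calculated", and the test is given as "groups compared using χ^2^ tests (two-sided p values reported". Neither this section nor any other part of the article brings district into an analysis. At 6 and 12 months, when group Z has no swabs, groups V and W combined stand in as the unvaccinated comparator.

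The Sample size section claims "82% power to detect a 40% reduction in the vaccinated group" for each schedule against control, assuming 15% carriage in controls and 10% loss to follow-up.

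**The concern.** The usual principle is to analyse as randomised. Blocks within district hold the group proportions nearly constant across districts, so differences in carriage between districts largely cancel out of each comparison between groups. The crude chi-square and the crude interval do not know this: they use the overall binomial variance, which contains the between-district part as well as the within-district part. If districts differ, the reported standard error is larger than the true one, the test rejects less often than 5% under the null, and some power is lost on each of the four coprimary comparisons.

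The article names both the estimator and the test, so this is a stated method and not a detail left open for the analysis plan.

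**Working it through.** **Inputs.** From Sample size: 400 per vaccinated group and 900 controls; 10% loss leaves 360 and 810; control carriage 15%; a 40% reduction gives 9%; two-sided alpha 5%. From Study setting: three districts. The documents give no carriage by district, so the district prevalences below are assumptions, as are equal district sizes, exact 270:120 balance within each district and a common prevalence ratio of 0.6.

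**The plan's own figure.** For the unstratified two-proportion test:

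- Pooled prevalence = (810 × 0.15 + 360 × 0.09)/1170 = 0.1315.
- Null SE = √[0.1315 × 0.8685 × (1/810 + 1/360)] = 0.02141.
- Alternative SE = √[0.15 × 0.85/810 + 0.09 × 0.91/360] = 0.01962.
- Power = Φ[(0.06 − 1.96 × 0.02141)/0.01962] = Φ(0.92) = 82.1%.

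The stated 82% is reproduced, so the sample size and the crude analysis agree with each other.

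**True size of the crude test.** Under the null, the ratio of true to crude SE is r = √[mean of p(1 − p) over districts / P(1 − P)], where P = 0.15 and P(1 − P) = 0.1275. The size is 2Φ(−1.96/r).

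- 10/15/20%: mean = (0.0900 + 0.1275 + 0.1600)/3 = 0.1258; r = 0.993; size 4.85%.
- 5/15/25%: mean = (0.0475 + 0.1275 + 0.1875)/3 = 0.1208; r = 0.974; size 4.41%.

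**Power, crude against stratified.** Both use the true within-district SE in the denominator. They differ only in the null SE, which for the stratified test averages the pooled p(1 − p) over districts.

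- 10/15/20%: true SE 0.01952; null SE 0.02141 crude, 0.02129 stratified. Power is Φ(0.924) = 82.2% against Φ(0.936) = 82.5%.
- 5/15/25%: true SE 0.01924; null SE 0.02141 crude, 0.02092 stratified. Power is Φ(0.938) = 82.6% against Φ(0.987) = 83.8%.

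| Assumed control prevalence by district | Size of crude test | Crude power | Stratified power |
|---|---|---|---|
| 15/15/15% | 5.00% | 82.1% | 82.1% |
| 12/15/18% | 4.95% | 82.2% | 82.3% |
| 10/15/20% | 4.85% | 82.2% | 82.5% |
| 7.5/15/22.5% | 4.67% | 82.4% | 83.1% |
| 5/15/25% | 4.41% | 82.6% | 83.8% |

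**Check by simulation.** With 300,000 simulated trials per scenario there was no difference at 15/15/15%. At 10/15/20% the size was 4.87% and power 82.5% against 82.8%. At 5/15/25% the size was 4.43% and power 82.7% against 83.9%. These agree with the formulas.

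**The estimate itself.** In a separate run of 200,000 replicates at a prevalence ratio of 0.6, the empirical SD of the log prevalence ratio was the same for the crude and the Mantel-Haenszel estimate: 0.1905 for both at 10/15/20%, 0.1879 for both at 5/15/25%. Only the reported SE differs. Its mean was 0.1893 crude against 0.1885 stratified (0.4% smaller) at 10/15/20%, and 0.1893 against 0.1861 (1.7% smaller) at 5/15/25%. Coverage of the crude 95% interval at 5/15/25% was 95.5 to 95.8%, against 95.1 to 95.2% for the stratified interval.

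**The case against.** The strongest reply is that nothing in the article is wrong. The power figure and the crude test match, the test is valid, and any error is on the safe side. The three districts lie in one city, no district carriage is reported, and the largest effect above needs a fivefold spread. Adjustment for strata may also be in an analysis plan that is not shown. All of this stands, and it limits the point to a minor improvement. It does not remove it: the article commits to a crude analysis, and analysing by the randomisation strata costs nothing.

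Three stronger readings are tempting and are not supported.

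- **That the error bars are wrong as a matter of fact.** They are too wide only if carriage differs by district, which the documents do not show.
- **That precision of the estimate is thrown away.** With balanced allocation the crude and stratified estimates vary equally; the design has already delivered the precision.
- **That incomplete blocks could unbalance the comparison materially.** The 4:4:4:4:9 ratio needs at least 25 children per block to hold exactly (4 + 4 + 4 + 4 + 9), and the block size is not stated. With blocks of 25, at most one block per district is incomplete, among about 833 children (2500/3) if districts are equal. That imbalance is trivial. Loss to follow-up could also disturb balance, but the documents give nothing from which to size it, and the calculations above assume balance.

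The remedy also has a trap. A continuity-corrected Cochran-Mantel-Haenszel test has only about 80% power at 10/15/20%, less than the planned chi-square, so the uncorrected version must be named.

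**Conclusion.** The mismatch between design and stated analysis is real, and its consequence is small and conditional. If district carriage in controls were 10/15/20%, the crude test would have a size of about 4.9% and lose about 0.3 percentage points of power. At an extreme 5/15/25% it would be about 4.4% and 1.2 points. With equal carriage there is no loss. The direction is conservative throughout, so no primary conclusion is threatened and the 82% power claim stands. These sizes rest on the assumed district prevalences, equal districts, balanced retention and a common prevalence ratio.

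**What to change.** Replace the crude analysis by a Mantel-Haenszel prevalence ratio with 95% CI and a Cochran-Mantel-Haenszel test without continuity correction, both stratified by district. Log-binomial or modified Poisson regression with district as a factor is an acceptable alternative; choose one and name it before analysis. Apply it to each comparison with group Z at 18 and 24 months. At 6 and 12 months apply it to the comparisons with groups V and W combined, since Z is not swabbed then. Keep the crude prevalence ratio as a descriptive check.

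The cost is a sentence or two of wording. No new data are needed, because allocation is by district and so district is known for every child, and three large strata raise no sparse-data problem. If the analysis plan already adjusts for district, it is enough to bring the published wording into line with it.

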#### Secondary objectives

To evaluate the immunogenicity of a 1+1 schedule of PCV10 or PCV13.To evaluate the immunogenicity of a 0+1 schedule of PCV10 or PCV13.To determine whether the response to a dose of PCV10 or PCV13 at 12 months of age is enhanced by a dose at 2 months of age (ie, 0+1 vs 1+1).To investigate the kinetics of the immune response to PCV vaccination at 12 months of age, comparing antibody levels and memory B cell responses 7 days and 28 days postvaccination.To examine the serotype profile of transferred maternal pneumococcal antibodies at 2 months of age.To directly compare PCV10 and PCV13 in terms of immune responses and effect on NP carriage.

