#### Secondary immunological outcome measures

Serotype-specific IgG antibody concentrations for all PCV13 serotypes, measured by ELISA^17^ from all blood samples.Opsonisation indices (OI) for all PCV13 serotypes, measured by opsonophagocytic assay (OPA)^18^ for 50 participants per intervention group (groups V–Y) pre and 4 weeks post-12 months dose of PCV.Polysaccharide-specific memory B cells for serotypes 1, 5, 6A, 6B, 14, 19A and 23F, enumerated by ELISPOT^19^ for 50 participants per intervention group (groups V–Y) pre, 7 days post and 28 days post-12 months dose of PCV and at 24 months of age.

An overview of the procedures for collection, transportation and laboratory analyses of the blood and NP samples can be found in online supplemental appendix 2.

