### Participant timeline

Participants are enrolled at 2 months of age and followed up to 24 months of age (table 1). Group V–Y participants provide NP swabs at 6 and 12 months of age, and all participants provide NP swabs at 18 and 24 months of age for analysis of the NP carriage outcomes. A subset of 200 participants per group will be included in the immunology substudy and provide three (groups V–Y) or one (group Z) blood sample(s) over the course of the trial for analysis of vaccine responses (table 2).

**Table 1 T1:** Schedule of enrolment, interventions and assessments

Age (months)	2 months	3 months	4 months	6 months	12 months	18 months	24 months
Enrolment							
Informed consent	✓						
Eligibility assessment	✓						
Allocation	✓						
Interventions							
PCV10	X				V, X		Z
PCV13	Y				W, Y		
Infanrix-hexa	✓	✓	✓			✓	
Assessments							
Demographics	✓						
Household characteristics	✓						
Nasopharyngeal swab				V-Y	V-Y	✓	✓
General health	✓	✓	✓	✓	✓	✓	✓

✓Indicates applies to all groups (V–Z), otherwise group(s) specified.

PCV, pneumococcal conjugate vaccine.

**Table 2 T2:** Schedule of blood samples for immunology substudy (subset of groups V–Z)

Age (months)	2 months	3 months	12 months	Post-12 months*	24 months
Subgroup a			V-Y†	V-Y	V-Y
Sample volume			7.5 mL	2 mL	3.5 mL
Assays			ELISA, B cell	ELISA	ELISA
Subgroup b	V	W-Y	V-Y	V-Y	
Sample volume	2 mL	2 mL	2 mL	7.5 mL	
Assays	ELISA	ELISA	ELISA	ELISA, B cell	
Subgroup c			V-Y	V-Y	V-Y
Sample volume			3.5 mL	7.5 mL	3.5 mL
Assays			ELISA	ELISA, B cell	ELISA
Subgroup d			V–Y	V–Y	V–Y
Sample volume			3.5 mL	3.5 mL	7.5 mL
Assays			ELISA, OPA‡	ELISA, OPA	ELISA, B cell
Subgroup Z-I					Z
Sample volume					3.5 mL
Assays					ELISA

*The post-12 months blood sample is collected at 12 months plus 7 days in subgroups a and b and at 12 months plus 28 days in subgroups c and d.

†3.5 mL sample for ELISA only in group W.

‡OPAs not performed in group W.

OPA, opsonophagocytic assay.

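### Post-dose IgG is to be compared by plain t-test; for day 7 v day 28 and for V v W, adjusting for the scheduled 12-month pre-dose IgG would gain precision

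*Protocol article*

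**What the plan says.** The section on analysis of primary and secondary outcomes gives one rule for all immunological means: "Means will be compared using t-tests", with Fisher's exact test for proportions. The effect measures come just before it: "GMC and GMOI ratios and risk differences with 95% CIs will also be calculated". No covariate is mentioned.

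The secondary objectives include the kinetics of the response to the 12-month dose, "comparing antibody levels and memory B cell responses 7 days and 28 days postvaccination", and a direct comparison of PCV10 with PCV13.

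On sampling, the secondary immunological outcome measures list "Serotype-specific IgG antibody concentrations for all PCV13 serotypes, measured by ELISA^17^ from all blood samples". Table 2 shows an ELISA at 12 months in all four subgroups (a to d) of groups V to Y, then one post-dose sample per child. The table note reads "The post-12 months blood sample is collected at 12 months plus 7 days in subgroups a and b and at 12 months plus 28 days" for the other two subgroups. Where group W departs from the scheme in subgroup a, the IgG measurement is kept: "3.5 mL sample for ELISA only in group W". Group Z gives a single sample, at 24 months.

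**The concern.** A child has either a day-7 or a day-28 sample, never both, so the kinetics comparison cannot be paired within a child. V v W is also between children. In both, the differences between children in IgG before the dose stay in the error term of a two-sample t-test, although that level is measured by design. At stake is the width of the intervals for the IgG part of two secondary objectives. A chance imbalance in pre-dose IgG for one of the 13 serotypes would also remain in that serotype's GMC ratio.

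**Working it through.** **Is there a figure in the plan to reproduce?** Not for immunology. The only power statement is 82% for vaccine-type carriage at 24 months. With 10% loss (810 controls, 360 vaccinated), 15% v 9%, two-sided 5% and pooled variance under the null:

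- pooled proportion = (810 × 0.15 + 360 × 0.09)/1170 = 0.1315
- null SE = 0.0214; alternative SE = 0.0196
- power = Φ((0.06 − 1.96 × 0.0214)/0.0196) = 82.1%

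The figure reproduces, but it says nothing about the IgG comparisons.

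**Is the 12-month IgG a legitimate covariate?**

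- *Pre-dose.* Memory B cells are described as measured "pre, 7 days post and 28 days post-12 months dose of PCV and at 24 months of age", and the 12-month IgG comes from the same visit. Table 2 puts the post-dose sample in its own column. I read the 12-month sample as pre-dose in all four subgroups.
- *Day 7 v day 28 within a group.* The Allocation section says the subgroups are randomised in equal ratio. When a later sample is taken cannot change an earlier level. Legitimate.
- *V v W.* Both groups get their first study PCV at 12 months. Legitimate.
- *0+1 v 1+1, and X v Y.* The 2-month dose acts on the 12-month level. Adjusting would remove part of the effect under study. Not legitimate.
- *Memory B cells.* Table 2 has a 12-month B cell sample in subgroup a only, and not in group W. No usable baseline.

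**Numbers per arm.** 200 sub-study children per group over four equal subgroups is 50 each, so a+b = 100 and c+d = 100. V v W is likewise 100 v 100 at each post-dose time.

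**Size of the gain.** Let ρ be the correlation of log pre-dose with log post-dose IgG. The documents do not give it, so a range is shown.

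- variance factor = 1 − ρ²
- interval width factor on the log scale = √(1 − ρ²)
- equivalent number per arm = 100/(1 − ρ²)
- power, for a difference that the t-test detects with 80% power = Φ(2.80/√(1 − ρ²) − 1.96)
- GMC ratio detectable with 80% power = 10^(2.80 × 0.45 × √(2/100) × √(1 − ρ²)), with an assumed log10 SD of 0.45

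| ρ | Variance reduction | Interval width × | 100 per arm acts like | Power | Detectable GMC ratio |
|---|---|---|---|---|---|
| 0 | 0% | 1.00 | 100 | 80% | 1.51 |
| 0.2 | 4% | 0.98 | 104 | 82% | 1.50 |
| 0.3 | 9% | 0.95 | 110 | 84% | 1.48 |
| 0.5 | 25% | 0.87 | 133 | 90% | 1.43 |
| 0.6 | 36% | 0.80 | 156 | 94% | 1.39 |

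**Check by simulation** (3,000 runs per ρ, 90 per arm, same SD, baseline as the only covariate). At ρ = 0, 0.3 and 0.5 the ratio of adjusted to unadjusted variance was 1.00, 0.91 and 0.75. Power went from 78% (t-test) to 78%, 82% and 87%. Nothing material is lost when the baseline carries no information.

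**The case against.** The strongest reply is that nothing here is wrong. A comparison of mean log IgG between randomised arms is unbiased with the correct type I error, the endpoints are secondary, and no immunology power target exists for the t-test to miss. A condensed article that names one test does not forbid an adjusted model in an analysis plan that is not shown. The first part stands in full: a reader might infer that the t-test is invalid or biased, and the article does not support that. The second part has less force, because the article does name the test for all immunological means, and a better one is available from samples already scheduled.

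The size of the gain is also open. In V and W the 12-month level precedes any study PCV, so it may predict the response to a first dose poorly, and the correlation may differ between day 7 and day 28. This stands. It is why the range starts at zero, and at ρ of 0.2 to 0.3 the gain is modest.

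The change is not entirely free. V v W and X v Y serve one objective but would be analysed by different models, so the two PCV10 v PCV13 contrasts would no longer be strictly parallel. A complete-case adjusted model would also drop a child who has a post-dose but no pre-dose result, which fits badly with the planned intention-to-treat population. The first is a small real cost; the second is avoidable.

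**Conclusion.** The point holds as a loss of precision, limited to post-dose IgG in two comparisons: day 7 v day 28 within each of groups V to Y, and V v W after the 12-month dose. The variance given up is ρ², from 0% at ρ = 0 to 36% at ρ = 0.6. This rests on an assumed correlation, on analysis of log IgG (implied by the GMC ratios), and on about 100 children per arm before losses.

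Three wider readings are not supported. A reader might take it that every sub-study child has a 12-month baseline; the 200 in group Z do not, though they enter neither comparison. A reader might think both secondary objectives are affected as a whole; kinetics also covers memory B cells, and the vaccine comparison also covers X v Y and carriage, none of which gains. And a reader might want to adjust every immunological comparison for the 12-month level, which would be a mistake wherever the 2-month dose separates the arms.

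**What to change.** In the statistical methods, for post-dose IgG in day 7 v day 28 within each group and in V v W after the 12-month dose:

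- Replace the t-test with a linear model on log post-dose IgG, with log 12-month pre-dose IgG and district (the randomisation stratifier) as covariates. Report the adjusted GMC ratio with its 95% CI.
- Keep children with a missing pre-dose value, for example by imputing the mean baseline of the compared arms combined or by a missing-value indicator. State which.
- Keep the unadjusted t-test as a sensitivity analysis. For V v W this also gives a result parallel to X v Y.
- State that 0+1 v 1+1 and X v Y are not adjusted for the 12-month level, and that memory B cell comparisons are unchanged.

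The cost is a few sentences of analysis wording. No visit, sample or assay is added.

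### Fisher's exact test for the immunology proportions is valid but conservative at 45–100 per group; an unconditional exact test would recover some power at no cost

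*Protocol article*

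**What the plan says.** The protocol article, under Analysis of primary and secondary outcomes, summarises IgG partly as "the proportion with protective antibody levels (≥0.35 µg/mL") and OPA partly as the proportion reaching an OI of at least 8. It adds that "GMC and GMOI ratios and risk differences with 95% CIs will also be calculated", without naming the interval method. The test is then fixed: "Means will be compared using t-tests and proportions compared using Fisher’s exact tests". The carriage proportions in the same section are compared by χ² tests.

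The sample sizes come from three places:

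- Participant timeline: "A subset of 200 participants per group will be included in the immunology substudy".
- Allocation: groups V–Y are "further randomised into one of four subgroups (a, b c or d) in an equal allocation ratio", which gives 50 per subgroup.
- The Table 2 footnotes: the timing of the post-12-month blood draw differs by subgroup, namely "collected at 12 months plus 7 days in subgroups a and b and at 12 months plus 28 days in subgroups c and d", and OPA is not performed in group W.

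Secondary immunological outcome measures describes OPA as being done "for 50 participants per intervention group (groups V–Y) pre and 4 weeks post-12 months dose of PCV", which does not carry the group W exception.

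**The concern.** In a randomised comparison the group sizes are fixed and the total number of responders is random. Fisher's test conditions on that total as well. Few p values are then attainable, and the rejection rate under no difference falls below 5%. The shortfall is largest when groups are small or the response proportion is near 1, and both are plausible for a threshold response after a PCV dose.

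Two consequences follow. Some power is lost in comparisons that serve named secondary objectives: 0+1 against 1+1, and PCV10 against PCV13. Also, the usual risk-difference intervals are not inversions of Fisher's test. A results table over 13 serotypes can therefore show an interval that excludes 0 beside p>0.05, with nothing in the text to say which governs.

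**Working it through.** **The plan's own power figure.** The only stated power is 82% for carriage (Sample size). After 10% loss the groups are 360 and 810, with rates of 9% and 15%.

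- Pooled rate = (810×0.15 + 360×0.09)/1170 = 0.1315.
- Null SE = √[0.1315×0.8685×(1/810+1/360)] = 0.0214.
- Alternative SE = √[0.15×0.85/810 + 0.09×0.91/360] = 0.0196.
- Power = Φ[(0.06 − 1.96×0.0214)/0.0196] ≈ 82%.

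The figure reproduces. It concerns the χ² primary analysis, and no power is stated for immunology.

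**Group sizes from Table 2 (groups V–Y).**

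- OPA (subgroup d, not group W) and 3-month IgG (subgroup b, groups W–Y): 50.
- Day-7 IgG (a+b) and day-28 IgG (c+d): 100 each.
- 24-month IgG (a, c, d): 150, with 200 in group Z.
- 12-month IgG (a–d): 200.
- With 10% loss, 50/100/150/200 become 45/90/135/180.

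**Assumptions.** Response rates are assumed, because the protocol gives none. A two-sided 5% level is carried over from the carriage calculation.

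**True size of Fisher's test.** Let P_F(x,y) be the two-sided Fisher p value for x/n against y/n. Size at a common rate p is the sum over all (x,y) of Bin(x;n,p)·Bin(y;n,p), restricted to tables with P_F ≤ 0.05.

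| n per group | p=0.80 | p=0.90 | p=0.95 |
|---|---|---|---|
| 45 | 2.6% | 2.0% | 0.6% |
| 50 | 2.8% | 1.8% | 0.7% |
| 90 | 3.2% | 3.0% | 1.9% |
| 100 | 3.3% | 2.9% | 2.1% |
| 180 | 3.7% | 3.2% | 2.7% |
| 200 | 3.7% | 3.4% | 2.9% |

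Over common rates from 0.50 to 0.95 the highest size is 3.5% at n=50, 4.0% at n=100, 4.3% at n=150 and 4.0% at n=200.

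**Power against Boschloo's test.** Boschloo rejects when P_F ≤ c, where c is the largest cut-off that keeps the size at or below 5% for every p. The cut-offs are about 0.075 (n=45), 0.069 (n=50), 0.067 (n=90), 0.064 (n=100), 0.062 (n=150) and 0.057 (n=200). Each exceeds 0.05, so Boschloo rejects whenever Fisher does.

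| n | Assumed rates | Fisher | Boschloo | Gain (points) |
|---|---|---|---|---|
| 45 | 80 v 95% | 48.0% | 55.2% | 7.2 |
| 45 | 60 v 80% | 46.4% | 54.7% | 8.3 |
| 45 | 70 v 85% | 30.4% | 38.8% | 8.4 |
| 50 | 80 v 95% | 50.8% | 58.3% | 7.5 |
| 50 | 67 v 90% | 75.7% | 80.1% | 4.4 |
| 90 | 70 v 85% | 61.8% | 66.7% | 4.9 |
| 100 | 75 v 90% | 76.2% | 79.2% | 3.0 |
| 150 | 78 v 90% | 77.5% | 80.6% | 3.1 |
| 200 | 80 v 90% | 76.8% | 79.0% | 2.2 |

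The gain depends on the alternative. At n=50 it is about 3–5 points where power is already near 80%, and about 5–8 for the smaller differences examined. It is larger when one rate is near 98%.

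**Test against interval.** Take 45/50 v 37/50.

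- Difference = 0.90 − 0.74 = 0.16.
- Wald SE = √(0.90×0.10/50 + 0.74×0.26/50) = 0.0752, giving a CI of 1.3 to 30.7 points. Newcombe gives 0.8 to 30.7.
- Fisher p = 0.066.

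Two more tables behave the same way. 87/100 v 76/100 gives p=0.068 with Newcombe 0.2 to 21.6. 165/200 v 148/200 gives p=0.052 with Newcombe 0.4 to 16.5. For the assumed differences, Newcombe excludes 0 while Fisher's p exceeds 0.05 in about 7–11% of trials at 45–50 per group and 3–9% at 90–100.

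**What each alternative does to these tables.** Boschloo rejects the first (0.066 < 0.069) and third (0.052 < 0.057) but not the second (0.068 > 0.064), so it reduces the disagreement without removing it. The N-1 chi-square statistic is (N−1)(ad−bc)²/(product of the four margins). For the first table it is 99×(45×13−37×5)²/(50×50×82×18) = 4.29. For the second it is 199×(87×24−76×13)²/(100×100×163×37) = 3.99. Both exceed 3.84, and the Miettinen-Nurminen interval excludes 0 exactly when this test rejects.

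**The case against.** The strongest reply is that nothing here is an error, and that is right. Fisher's test keeps type I error at or below 5%, the outcomes are secondary, and no stated power depends on it. A reader might infer from the low sizes that the trial's error control or its 82% power is wrong. Neither follows: the departure is conservative, and the 82% belongs to the χ² carriage analysis and reproduces.

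Using χ² for carriage and an exact test for immunology is not inconsistent either. Carriage compares about 360 with 810. At 50 per group and 95% response only 0.05×50 = 2.5 non-responders are expected per group, which is a normal reason to choose an exact test.

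Four further limits stand:

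- A reader might take the low sizes as typical of all the trial's comparisons. They are not: at 135–200 per group the loss against Boschloo is only about 0–4 points.
- A reader might say that Fisher contradicts the plan's own intervals. The article names no interval method, and an analysis plan that is not shown may name one that matches the test. The disagreement is shown only for common intervals such as Newcombe or Wald.
- Under the Table 2 footnote there is no OPA comparison involving group W, so OPA offers neither 0+1 v 1+1 for PCV13 nor PCV10 v PCV13 within 0+1.
- The 10% loss is stated for the 24-month carriage calculation. It may overstate loss in the 3-month sample, so results are given for 50 as well as 45.

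What remains is that the test is fixed in the text, and that another exact test holds the same 5% bound and rejects at least as often.

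**Conclusion.** The point holds as a low-severity efficiency and coherence improvement. The avoidable loss of power is concentrated in the comparisons at 45–50 per group, is moderate at 90–100, and is slight in the 12- and 24-month IgG comparisons. All the size, power and disagreement figures rest on assumed response rates and an assumed two-sided 5% level for immunology. The disagreement rates also rest on an assumed interval method. No conclusion about carriage is affected.

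**What to change.** In Analysis of primary and secondary outcomes, replace Fisher's exact test with Boschloo's exact unconditional test for the immunology proportions. It keeps size at or below 5% and rejects whenever Fisher does. It does not by itself guarantee that the p value agrees with the risk-difference CI.

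If that agreement is the priority, specify instead the N-1 chi-square test with the matching Miettinen-Nurminen CI. The price is a size slightly above 5% at some rates in small groups (up to 5.7% at n=50).

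Either choice is one line of text, to be settled before the immunology data are analysed. It needs no new data, participants or visits.
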